### Data management

2.5

Data are collected using Castor EDC [23], a secure, cloud-based electronic data capture platform with an audit trail. Data is coded, pseudonymized, and stored in accordance with General Data Protection Regulation guidelines to ensure participant confidentiality [24]. To promote data quality and minimize interobserver variability, all assessors received comprehensive training on the study protocol and data entry procedures and Standard Operating Procedures (SOPs) are in place. Quality control measures such as automated range checks are employed to identify and correct discrepancies. Access to the database is restricted to authorized personnel only. Data are handled in accordance with a predefined data management plan, which includes protocols for secure storage, access, and continuous quality monitoring.

### Statistical analysis

2.6

Data will be analyzed according to the intention-to-treat principle. Baseline characteristics will be presented as numbers and percentages for categorical variables and as medians with interquartile ranges for non-normally distributed continuous variables. Categorical variables will be compared using Pearson's chi-squared or Fisher's exact test, and continuous variables using the Kruskal–Wallis test. The primary analysis will evaluate the diagnostic performance of the HEART-GP strategy in terms of diagnostic metrics, focusing primarily on safety, defined by sensitivity and negative predictive value for ruling out 6-week MACE, and efficiency, defined as the proportion of patients classified as low-risk. Secondary analyses will compare the diagnostic performance of the *HEART-GP strategy* with current standard care based on unaided clinical judgment, evaluate whether sex-specific hs-troponin cut-offs improve efficiency without compromising safety, and assess whether incorporating hs-troponin measurements into established clinical risk scores (HEART, INTERCHEST, and Marburg Heart Score) further improves diagnostic accuracy. Discriminatory ability for HEART-GP and comparator scores will be quantified using the area under the receiver operating characteristic curve (AUC). Differences in discriminatory performance will be tested using the DeLong method and the Net Reclassification Improvement (NRI). An exploratory analysis will examine the added value of including ECG findings in a modified HEART score. Missing data will be addressed through multiple imputation to ensure robustness of estimates.

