**Methods and analysis:**

This multicenter prospective diagnostic accuracy trial evaluates the *HEART-GP strategy*, combining a single fingerstick hs-troponin test with clinical assessment and optional ECG. Adults (≥18 years) presenting with acute chest pain or discomfort to one of four participating Dutch OOH-PC centers are eligible. The primary outcome is the occurrence of major adverse cardiovascular events a composite of death, ACS, or urgent revascularization within six weeks. Diagnostic safety (sensitivity, negative predictive value) and efficiency (ED referral reduction) will be compared against standard care. Secondary analyses will assess the value of sex-specific cut-offs and integration with existing risk scores.

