### Objectives

1.2

To address this gap, we are conducting a diagnostic trial evaluating a primary care-tailored approach for ruling out ACS in OOH-PC that balances diagnostic safety and efficiency. Our primary objective is to evaluate the diagnostic performance of the *HEART-GP strategy*, which integrates a single fingerstick-obtained hs-troponin measurement with clinical assessment and an optional ECG, in terms of safety (sensitivity and negative predictive value) and efficiency (reduction in ED referrals) when used in out-of-hours primary care. The primary outcome is major adverse cardiovascular events (MACE), a composite of death, ACS, or urgent revascularization within six weeks of index presentation, reflecting the risk for cardiovascular events rather than a single clinical syndrome.

The secondary objectives are:1.To compare the diagnostic performance (safety and efficiency) of the *HEART-GP strategy* with current standard care based on (unaided) clinical judgment.2.To evaluate whether using sex-specific versus universal hs-troponin cut-off values improves safety and/or efficiency.3.To assess whether embedding hs-troponin measurements in established clinical risk scores (HEART, INTERCHEST, Marburg Heart Score) further improves diagnostic performance compared to the HEART-GP strategy alone.

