**Fig. 3 fig3:**
[figure not shown]
HEART-GP strategy GP: general practitioner, hs-cTnI: high-sensitivity cardiac troponin, POCT: point-of-care test, ACS: acute coronary syndrome.

All (triage) nurses at the participating OOH-PC centers receive standardized training by study personnel to ensure correct execution of the POCT, including sample collection, device operation, and interpretation of results. In the event of a test error, nurses are instructed to repeat the measurement using a maximum of two cartridges. A detailed testing protocol is included in Appendix 1.

The *HEART-GP strategy* guides decision-making on whether to refer the patient to the (cardiac) ED or manage them in primary care. As part of this strategy, it is of importance to note that the GPs' clinical judgement is paramount in deciding on the treatment plan. For instance, even if a patient's hs-troponin POCT value is below the cut-off of 4 ng/L, based on the discretion of the GP the patient may still be referred.

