#### Symptom assessment form

2.2.2

The treating physician is asked to complete a structured, symptom-based checklist designed to standardize and document clinical assessment. The form includes symptom elements of three risk scores, namely (modified) H(E)ART, INTERCHEST and the Marburg Heart Score (Table 1). In addition, GPs are asked to record their ‘gut feeling/sense of alarm’, as well as whether they would have referred the patient based on their clinical judgement without access to the POCT result. The checklist is completed during the index consultation, instructed to be completed prior to disclosure of troponin result, to ensure unbiased responses. The form contains no recommendations or prompts regarding management decisions.

**Table 1 tbl1:** (Modified) HEART(s), Marburg Heart Score, INTERCHEST risk stratification scores.

(Modified) HEART score [16,17]		Points	Marburg Heart Score [18]		Points	INTERCHEST [19]		Points
History	Highly suspicious	2	Sex/age (Female ≥65, male ≥55 years)	Yes	1	Sex/age (Female ≥65, Male ≥55 years)	Yes	1
	Moderately suspicious	1		No	0		No	0
	Slightly suspicious	0						
ECG	Significant ST deviation	2	History of cardio-vascular disease	Yes	1	History of coronary artery disease	Yes	1
	Non-specific repolarization abnormalities	1		No	0		No	0
	Normal	0						
Age	≥65 years	2	Patient assumes the pain is of cardiac origin	Yes	1	Chest pain related to effort	Yes	1
	45 – 64 years	1		No	0		No	0
	<45 years	0						
Risk factors	History of atherosclerotic disease or ≥ 3 RF	2	Pain gets worse with exercise	Yes	1	Pain reproducible by palpation	Yes	Minus 1
	1 – 2 RF	1		No	0		No	0
	No known RF	0						
Troponin∗	≥23 ng/L (99th percentile)	2	Pain is not reproducible by palpation	Yes	1	Physician initially suspected a serious condition	Yes	1
	4-23 ng/L	1		No	0		No	0
	<4 ng/L	0						
∗Sex-specific HEARTs: sex-specific 99th percentile for troponin (male 27 ng/L, female 18 ng/L) [15]						Chest discomfort feels like pressure	Yes	1
							No	0

Table 1: *ECG: electrocardiogram, RF: risk factors for atherosclerosis, HEART: History, ECG, Age, Risk Factors, Troponin, INTERCHEST: international chest pain prediction*.

Non-specific repolarization abnormalities: LVH: left ventricular hypertrophy, LBBB: left bundle branch block or PM: pacemaker.

Risk factors: Hypertension, Hypercholesterolemia, Diabetes Mellitus, obesity (BMI >30 kg/m2), smoking, positive family history.

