#### Index contact

2.4.1

The study workflow is described in Fig. 2, Fig. 4. In short, during the consultation the patient receives information about the study's objectives, procedures, potential risks and benefits, and decides on their participation. Upon agreement, initial informed consent is obtained by the treating physician, and hs-troponin POCT is conducted by a trained (triage) nurse. While the POCT runs, the GP completes the ‘*chest pain assessment form*’. Subsequently, the GP determines the treatment plan ((e.g. discharge with safety-net advice (‘watchful waiting’), consulting a cardiologist or referral to the hospital for further assessment)). At all times, the GP's own clinical judgement serves as the guiding principle in the management following the consultation. For safety reasons, urgent referral is advised in cases of high clinical suspicion of ACS, hs-troponin POCT values ≥ 4 ng/L, and/or an abnormal ECG (if performed), in line with the HEART-GP strategy recommendations. Additionally, GPs are informed to refer all patients with troponin levels exceeding the overall 99th percentile of 22.9 ng/L. Patients who refuse study participation receive routine care only, which focuses on history taking, physical examination and, based on the discretion of the GP, potentially an ECG, as this is not a part of the standard work-up of chest pain in Dutch primary care [6].

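### The primary objective states efficiency as a reduction in ED referrals in use, but the primary analysis measures the share classified low-risk, which has no comparator and counts no referrals

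*Protocol article*

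**What the plan says.** The protocol article gives efficiency two meanings.

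- **Section 1.2, primary objective:** "efficiency (reduction in ED referrals) when used in out-of-hours primary care".
- **Abstract, Methods and analysis:** "efficiency (ED referral reduction) will be compared against standard care".
- **Section 2.6, primary analysis:** "efficiency, defined as the proportion of patients classified as low-risk".

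A comparison with usual care is planned as a secondary objective, which opens "To compare the diagnostic performance (safety and efficiency) of the" HEART-GP strategy and names unaided judgement as the other side. Section 2.6 repeats the plan: "Secondary analyses will compare the diagnostic performance of the *HEART-GP strategy* with current standard care based on unaided clinical judgment". It attaches no separate efficiency measure to that comparison. The data for the comparator come from the form in section 2.2.2, on which the GP records "whether they would have referred the patient based on their clinical judgement without access to the POCT result". The form is meant to be filled in before the result is known.

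Management is left to the GP. Under section 2.2.1, for a value below the cut-off, "based on the discretion of the GP the patient may still be referred". Under section 2.4.1 urgent referral of flagged patients is advised, while the GP's "own clinical judgement serves as the guiding principle in the management following the consultation".

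**The concern.** A reduction needs two quantities: referrals without the strategy and referrals with it. The low-risk share is neither. Its complement is the referral rate that would arise if every GP did what the classification indicates. It equals the actual rate only if GPs never depart from the classification or their departures cancel.

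The case for the strategy in section 1.1 rests on actual referrals: high referral rates, ambulance use, ED workload and cost. If the analysis is run as section 2.6 words it, the efficiency half of the primary objective is not estimated as stated. A later claim of fewer ED referrals in practice could then rest on referrals that the classification would have spared but GPs still made. The reverse error is also possible.

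**Working it through.** **1. The plan's own figure.** Section 2.6.1 gives 842 participants from sensitivity 98%, margin 3%, two-sided alpha 0.10 and MACE prevalence 7%. The precision formula gives 1.645² × 0.98 × 0.02 / 0.03² = 58.92 events, and 58.92 / 0.07 = 841.7, so 842. The figure reproduces. It depends on sensitivity alone, so nothing below changes it or the target of 900.

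**2. Inputs for the efficiency check.**
- From the article: n = 900 (section 2.6.1), and a current referral rate of 40–70% (section 1.1).
- Assumed, because the article gives no values: low-risk share L; share a of low-risk patients referred anyway; share b of flagged patients not referred; discordance d between the two decisions; and an unaided referral rate U of 55%, the middle of the 40–70% range.

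**3. Indicated and actual referral.**
- Indicated rate = 1 − L.
- Actual rate = L·a + (1 − L)(1 − b).
- Gap (actual minus indicated) = L·a − (1 − L)·b.

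The gap is zero only if a = b = 0 or the two terms cancel.

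**4. Size of the gap in 900 patients.**

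| Assumed L | a = 10%, b = 0 | a = 0, b = 10% |
|---|---|---|
| 30% | +27 referrals (3 points) | −63 (7 points) |
| 50% | +45 (5 points) | −45 (5 points) |
| 70% | +63 (7 points) | −27 (3 points) |

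**5. Effect on a claimed reduction.** Take U = 55% and L = 60%. The indicated reduction is 55 − 40 = 15 points (135 patients).
- a = 20%, b = 0: actual rate 0.60 × 0.20 + 0.40 = 52%; reduction 3 points (27 patients).
- a = b = 10%: actual rate 0.06 + 0.36 = 42%; reduction 13 points (117).
- a = 0, b = 20%: actual rate 0.40 × 0.80 = 32%; reduction 23 points (207).

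The indicated figure can therefore err in either direction.

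**6. Against sampling error.** The 95% half-width of a paired difference is at most 1.96 × √(d/900).
- d = 10%: 2.07 points.
- d = 25%: 3.27 points.
- d = 40%: 4.13 points.

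A net gap of 5 points exceeds all three. A gap of 3 points exceeds only the first.

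**The case against.** **The low-risk share suits a diagnostic accuracy design.** This stands. It is also the only measure that applies equally to the sex-specific cut-offs and the risk scores, since the article does not say that GPs act on those. The fault is the mismatch with the objective, not the metric.

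**GP discretion is part of the strategy.** This stands in part. Section 2.2.1 presents the GP's judgement as belonging to the strategy, and section 2.4.1 makes high clinical suspicion a reason to refer in its own right. A patient below 4 ng/L who is referred on suspicion may therefore not count as low-risk, and a could be small. The algorithm figure is not available to settle this. It does not affect flagged patients who are not referred, and it does not turn a single share into a reduction.

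**The secondary comparison may use actual referrals.** A reader might infer that this comparison is bound to yield only strategy-indicated referrals avoided. The article does not support that as fact: section 2.6 ties its definition to the primary analysis, and the abstract's wording leaves room for a referral-based comparison. What can be said is that no other measure is stated and no analysis of actual referrals is mentioned. The unseen full protocol or SAP could excuse silence, but here the article itself gives two different definitions.

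**Actual referral is an imperfect measure too.** This stands. The comparator is an intention, and in-trial referrals are shaped by the study's safety advice. That is a reason to report both measures.

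**Conclusion.** The mismatch is real and lies in the current text. The objective concerns a change in ED referrals when the strategy is used; the primary analysis reports a classification share. Followed as written, the primary analysis does not estimate that half of the primary objective.

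The size and direction of the difference are unknown. Only the 900 patients and the 40–70% referral range come from the article; every other input is assumed. On those assumptions, 10% of departures in one direction moves 27 to 63 referrals (3 to 7 points), and 45 (5 points) at a 50% low-risk share. A reader might infer that the low-risk share will overstate the benefit, or that the true reduction could be nil. The article supports neither: departures are possible in both directions, and no departure rate is given. The change should be made, but it does not touch the safety estimates.

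**What to change.** In section 2.6:

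1. Label the low-risk share as potential (rule-based) efficiency, and keep it for comparing cut-offs and risk scores.
2. For the stated objective, add the paired difference, with a 95% confidence interval, between the proportion the GP would have referred before disclosure (section 2.2.2) and the proportion actually referred to the ED.
3. Report two counts: low-risk but referred, and flagged but not referred.
4. Base any claim of fewer ED referrals in practice on the paired difference, and state that its comparator is a recorded intention.

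Sensitivity and NPV stay rule-based. The cost is one redefinition and one extra analysis, with no new patients or procedures. Final disposition may have to be taken from the general-practice and hospital records already used under section 2.4.2. The resulting figure may be less favourable than the low-risk share.

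### Comparing the two-way HEART-GP rule with multi-level risk scores by AUC/DeLong, or by a summed NRI, can favour a score that is no safer or more efficient

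*Protocol article*

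**What the plan says.** Section 2.6 (Statistical analysis) defines performance by what happens at the rule-out decision: "safety, defined by sensitivity and negative predictive value for ruling out 6-week MACE", and "efficiency, defined as the proportion of patients classified as low-risk". Secondary objective 3 in section 1.2 is "To assess whether embedding hs-troponin measurements in established clinical risk scores (HEART, INTERCHEST, Marburg Heart Score) further improves diagnostic performance" relative to HEART-GP alone.

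For comparisons between strategies, section 2.6 names one metric and two methods: "Discriminatory ability for HEART-GP and comparator scores will be quantified using the area under the receiver operating characteristic curve (AUC"), and then "Differences in discriminatory performance will be tested using the DeLong method and the Net Reclassification Improvement (NRI"). It does not say how HEART-GP is coded for the ROC analysis or which type of NRI is meant.

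The description of HEART-GP points to a two-way output. Section 2.2.1 says that the strategy "guides decision-making on whether to refer the patient to the (cardiac) ED or manage them in primary care". In section 2.4.1, "urgent referral is advised in cases of high clinical suspicion of ACS", and likewise for a troponin value of at least 4 ng/L or an abnormal ECG, so any one positive element is enough. The comparators in Table 1 (section 2.2.2) are point scores.

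**The concern.** A rule with two outcomes has one operating point. A point score has several, and its AUC sums ranking ability over all of them, including cut-offs at which sensitivity would be far too low for ruling out MACE. When the two are set against each other by AUC and DeLong, the score can come out significantly better although it refers and rules out exactly the same patients.

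The question in objective 3 is whether a troponin-embedded score would be safer or more efficient than HEART-GP alone. The plan's own terms for that are sensitivity, NPV and low-risk proportion, and AUC measures none of them. At stake is a possible conclusion that a more elaborate score improves on the simple rule when the referral decisions are no better. A summed NRI could go further and favour a rule that misses more MACE.

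**Working it through.** **Inputs**
- Target sensitivity 0.98, margin 0.03, two-sided alpha 0.10, MACE prevalence 7%, at least 900 participants (section 2.6.1).
- Score ranges, summed from Table 1: HEART 0 to 10, Marburg 0 to 5, INTERCHEST −1 to 5.
- Specificity of HEART-GP: not in the article. Assumed range 0.30 to 0.70.

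**The plan's own figure.** Events needed = 1.6449² × 0.98 × 0.02 / 0.03² = 58.92. Dividing by 0.07 gives 841.7, which rounds up to the stated 842. At 900 participants one expects 900 × 0.07 = 63 events and 837 non-events.

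**AUC of a two-way rule against a graded score.** For a binary rule, AUC = (Se + Sp)/2. For an equal-variance binormal score passing through the same point, AUC = Φ((z(Se) + z(Sp))/√2). At Se 0.98 and Sp 0.50, the binary AUC is (0.98 + 0.50)/2 = 0.74. The graded AUC is Φ(2.054/1.414) = 0.927.

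| Assumed Sp | Binary AUC | Graded AUC, same cut | Gap |
|---|---|---|---|
| 0.30 | 0.64 | 0.860 | 0.22 |
| 0.40 | 0.69 | 0.899 | 0.21 |
| 0.50 | 0.74 | 0.927 | 0.19 |
| 0.60 | 0.79 | 0.949 | 0.16 |
| 0.70 | 0.84 | 0.966 | 0.13 |

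Sensitivity, NPV and low-risk proportion are identical within each row.

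**DeLong and NRI by simulation.** A 7-level score was compared with the same score cut once, in 400 runs with 63 events and 837 non-events, at specificity 0.40, 0.50 and 0.60. The mean AUC of the score was 0.890, 0.918 and 0.941, against 0.690, 0.741 and 0.790 for the binary version. DeLong gave p<0.05 in every run. The category-free NRI averaged about +0.82 in favour of the score. The two-category NRI at the shared cut was exactly 0.

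**How far this depends on the extra levels.** At Se 0.98 and Sp 0.50, a 10-level score that shares HEART-GP's cut but whose further levels carry no information had AUC 0.739, the same as the binary rule. DeLong was significant in 4.5% of runs, close to the nominal rate. With mildly informative levels (AUC 0.775) the figure was 47%, and at AUC 0.805 it was 95%.

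**The summed two-category NRI.** At fixed cuts it equals ΔSe + ΔSp. Moving from rule A to rule B gives (0.90 − 0.98) + (0.65 − 0.50) = +0.07.

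| | Rule A | Rule B |
|---|---|---|
| Se / Sp | 0.98 / 0.50 | 0.90 / 0.65 |
| One-cut AUC | 0.740 | 0.775 |
| Expected missed MACE among 63 | 63 × 0.02 = 1.3 | 63 × 0.10 = 6.3 |
| NPV at 7% prevalence | 0.465/0.4664 = 99.7% | 0.6045/0.6115 = 98.9% |
| Low-risk proportion | 46.6% | 61.2% |

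Both the one-cut AUC and the summed NRI prefer B, which misses about five more of the 63 events.

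**The case against.** - **Safety and efficiency are in the plan.** They are the primary estimates, and section 2.6 announces secondary comparisons of diagnostic performance. AUC, DeLong and NRI are attached to discrimination only. This stands: a reader might infer that objective 3 will be decided by AUC alone, but no sentence says so.
- **Unnamed details may lie elsewhere.** The article condenses a fuller protocol, and an analysis plan may exist. A paired test, a rule-out cut for each score and the NRI type could be set there, so their absence here is no error. Nor should one infer that independent-group tests will be used on paired classifications: the chi-squared, Fisher and Kruskal–Wallis tests appear with the baseline description.
- **NRI need not penalise a binary rule.** Correct for a two-category NRI, whose event component is simply the change in sensitivity. The remaining difficulty there is the equal weight given to the two components when they are summed.
- **AUC rewards informative levels, not the number of levels.** Also correct, as the 4.5% result shows. The extra ranking is genuine information; it is just not what a rule-out comparison asks about.
- **The numbers are constructed.** Specificity is assumed, and the binormal score is informative by design, so the 100% DeLong rate is not a forecast for this trial. The article gives no AUC for any of the scores.
- **Binary coding is inferred.** Fig. 3 is not shown, and section 2.4.1 also mentions a second troponin threshold of 22.9 ng/L. Even so, sections 2.2.1, 2.4.1 and 2.6 all describe a refer/low-risk classification.

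What survives is a mismatch between a stated method and the plan's own definition of performance.

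**Conclusion.** The point holds in limited form. If HEART-GP enters the ROC analysis as the two-way rule the article describes, AUC with DeLong can favour a graded score that is neither safer nor more efficient. The illustrative gap is 0.13 to 0.22 in AUC over assumed specificities of 0.30 to 0.70. It rests on the target sensitivity of 0.98 and an equal-variance binormal score, and it falls to zero if the further levels are uninformative. A category-free NRI has the same fault. A two-category NRI does not, but its sum can mask a loss of safety.

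This concerns a secondary objective, and the change is one that should be made. It does not show that the objective will be answered wrongly, that safety and efficiency go uncompared, or that the primary analysis or the figures of 842 and 900 are in doubt.

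**What to change.** For secondary objective 3, amend section 2.6 (or confirm in the analysis plan) as follows:

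1. Prespecify one rule-out cut per score, and compare each score with HEART-GP at that cut on the same patients. Give paired differences with confidence intervals for sensitivity (among MACE), NPV and low-risk proportion. McNemar's test or a paired interval serves for sensitivity.
2. Limit AUC and DeLong to comparisons among the multi-level scores or with continuous troponin, or label any AUC comparison involving HEART-GP as supplementary.
3. Report reclassification separately for events and non-events, with confidence intervals, in place of a test on the summed NRI.

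The cost is a change of analysis wording and the loss of a single summary number. No new data are needed, and the sample size is unchanged.
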